### Outcomes

#### Primary outcomes: screening and brief advice rates

PHCUs will be asked to screen all patients aged 18 years and over who attended the PHCU. These patients are defined as eligible patients.

Patients will be screened for hazardous and harmful alcohol consumption with AUDIT-C [32]. Screen positives, or at risk patients, are defined as those who scored ≥ 5 for men or ≥ 4 for women on AUDIT-C. Participating staff that have signed up to the study will be asked to deliver brief alcohol advice of 5 to 15 min duration to at-risk patients, with the length and format of the brief advice based on country-specific guidelines or, for Poland where national guidelines are lacking, the European guidelines developed by PHEPA [33]. Providers of PHCUs allocated to e-BI activity will be asked to refer patients to a computerized brief advice program, considered equivalent to providing brief advice. Besides counting referral rate to e-BI, actual e-BI log-in rates of patients will be collected.

Screening and brief advice will be measured at five timepoints: during the four-week baseline period, the three consecutive four-week blocks during the twelve week implementation period; and, the four-week follow-up period, which will occur during the seventh month after the end of the twelve-week implementation period using paper tally sheets, with the exception of Catalonia who will use their electronic patient records. The tally sheets include AUDIT-C scores (*i.e.*, identification of at risk patients) with additional table to indicate the type of brief advice that was delivered to the patients at risk. Gender and age of patients will be recorded as well as the name and profession of the provider.

The screening rate will be calculated as the number of completed screens divided by the total number of consultations of all patients eligible for screening (as defined above) per participating provider times 100. The brief advice rate will be calculated as the number of BIs delivered (received oral brief advice, and/or were given an advice leaflet, and/or were referred to the e-BI program, and/or were referred to another provider in or outside the practice), divided by the total number of screen positives per participating provider times 100. Information will also be collected on the number of screen negatives who received brief advice.

Screening and brief advice rates will be calculated at two levels: at an aggregate PHCU level for all participating providers in the PHCU; and, at an individual provider level for each participating and actively participating providers. Participating providers are defined as those who attended the first briefing, or who were identified as joining the study by the contact person of the PHCU at the first briefing. Actively participating providers are defined as those participating providers who completed at least one tally sheet or computerized record during one of the measurement periods.

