## Background

The European Union (EU) has the highest alcohol consumption of the world: in 2009, the average adult (aged 15+ years) alcohol consumption in the EU was 12.5 litres of pure alcohol [1]. A review showed that consumption above 20 to 30 grams of alcohol a day (two to three glasses of wine) increases an individual’s risks of mortality and morbidity [2,3]. However, people often overestimate the positive health effects of alcohol; in fact, only small amounts of alcohol have positive effects on health [2,3].

Alcohol consumption is the third world leading cause of diseases and premature death [1]. The costs related to alcohol are €125bn a year for health, welfare, employment, and criminal justice sectors as a consequence of alcohol-attributable disease, injury, and violence [4]. Therefore, individuals and society would benefit from effective preventive measures with respect to morbidity and mortality and social costs.

There is considerable evidence showing that early identification of hazardous and harmful alcohol consumption result in reduced alcohol consumption and improved health outcomes. Primary healthcare (PHC) is the primary point of contact for many people seeking healthcare. In this setting, screening [5] and brief intervention programs have proven to be effective in reducing alcohol consumption [6-10], with a mean reduction of 38 grams of alcohol per week (three to four glasses of wine) [10]. Although the evidence is still inconsistent about positive effects of nurse-led interventions [11,12], generally screening and brief interventions are provided by healthcare workers such as GPs, nurses, or psychologists [10]. The number needed to treat (NNT) in offering screening and brief interventions is eight (for every eight people treated one will change their behaviour) [13], which is relatively low compared to smoking cessation, which has a NNT of around 35 or higher [14]. Despite the evidence for efficacy and cost-efficacy of screening and brief interventions in PHC, these interventions are rarely implemented in routine practice [15]. Commonly, less than 10% of the population at risk are identified, and less than 5% of those who could benefit are offered screening and brief interventions in PHC settings [15].

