### Aim and objectives

Our aim is to study the effectiveness of training and support (T&S), financial reimbursement, and internet based brief interventions (e-BI), targeted singly or in combination to primary healthcare units, on screening and brief intervention activities, compared to treatment as usual. The following hypotheses will be tested in the study:

1. Provision of training and support to primary healthcare providers will increase use of preventive screening and brief interventions compared to a care as usual control group.

2. Financial reimbursement to primary healthcare providers as a pay-for-performance of brief alcohol interventions will increase screening and brief intervention rates compared to care as usual.

3. Providing resources, *i.e.*, offering referral possibility to an internet-based method of delivering brief intervention, will increase screening and brief intervention rates compared to care as usual.

4. The combination of training and support, financial reimbursement, and e-BI will be more effective in increasing screening and brief intervention rates compared to single-focused implementation strategies.

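### The primary brief advice rate is conditioned on screen positives, a group formed after randomisation that every strategy is meant to enlarge, so it can read as null or negative when more patients are advised

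*Protocol article*

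**What the plan says.** Two primary rates are defined under Outcomes (Primary outcomes: screening and brief advice rates), with different denominators:

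- **Screening rate:** completed screens "divided by the total number of consultations of all patients eligible for screening (as defined above) per participating provider times 100".
- **Brief advice rate:** brief interventions "divided by the total number of screen positives per participating provider times 100".

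The same section gives the entry condition for the second denominator: "Screen positives, or at risk patients, are defined as those who scored ≥ 5 for men or ≥ 4 for women on AUDIT-C". A patient who is not screened cannot be in it.

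Other parts of the article bear on how that denominator is formed:

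- **Aim and objectives:** training and support "will increase use of preventive screening and brief interventions compared to a care as usual control group". Financial reimbursement and e-BI are each expected to raise both rates; the wording for reimbursement is "will increase screening and brief intervention rates compared to care as usual".
- **Implementation strategies (Table 1):** the financial groups are paid for screening as well as for advice.
- **Randomization and blinding:** allocation is disclosed once baseline data are in, and practices and investigators are unblinded from then on.
- **Sample size:** screening is planned to rise from 8% to 12%, and brief advice from 4% to 6%. The denominator of the 4% and 6% is not stated.

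No rate of advice per eligible patient or consultation is defined.

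**The concern.** The denominator of a primary outcome is itself an outcome of the intervention. After baseline it is built up by providers who know their group, through the activity that the other primary outcome measures. The brief advice rate therefore answers whether a positive patient, once found, is advised. It does not answer whether the strategy leads to more at-risk patients being advised.

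The two answers can differ in sign. A strategy that finds more at-risk patients and follows them up equally well gets no credit on this outcome. One that follows up the additional patients somewhat less well is marked down, even though more people receive advice. The Background describes the problem as one of reach: "less than 5% of those who could benefit are offered screening and brief interventions in PHC settings". A policy reader could take a null or negative advice result as failure when it reflects success in screening.

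The Sample size section adds a second issue: its advice calculation appears to rest on a different denominator from the one defined under Outcomes.

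**Working it through.** **Inputs from the Sample size section.** Screening 8% to 12%; advice 4% to 6%; ICC 0.029; at least 1,000 eligible patients per PHCU per month; alpha 5%; power 80%; 56 and 120 PHCUs.

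**Assumptions, not in the document.** Two-sided test; factorial main effect (four groups v four groups, so 60 v 60 PHCUs); 10% to 40% of screens positive; one four-week period; one consultation per patient.

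**1. Reproducing the plan.** Design effect = 1 + (1000 - 1) × 0.029 = 29.971. The two-proportion formula with continuity correction gives:

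- Screening: 932 per side; 932 × 29.971 / 1000 = 27.93 PHCUs per side; 56 in total.
- Advice: 1,962 per side; 1,962 × 29.971 / 1000 = 58.80 PHCUs per side; rounded up to a multiple of eight, 120 in total (112 without continuity correction).

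Both stated figures reproduce, the second with 1,000 units per PHCU in the advice denominator. That is the number of eligible patients, not of screen positives.

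**2. The same comparison on the defined denominator.** Positives per PHCU: m = 1000 × screening rate × positivity. Effective number per side = 60m / (1 + (m - 1) × 0.029). For 4% v 6%, without continuity correction:

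| Screening | Positivity | m | Effective n per side | Power | PHCUs for 80% |
|---|---|---|---|---|---|
| 8% | 10% | 8 | 399 | 0.25 | 562 |
| 8% | 40% | 32 | 1,011 | 0.54 | 222 |
| 12% | 10% | 12 | 546 | 0.33 | 410 |
| 12% | 40% | 48 | 1,219 | 0.62 | 184 |
| eligible patients | – | 1,000 | 2,002 | 0.83 | 112 |

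**3. When the rate and the number advised disagree.** Number advised = eligible × screening × positivity × advice rate. With equal positivity, strategy over control = (0.12 × a1) / (0.08 × a0) = 1.5 × a1/a0.

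- If a1 = a0, the number advised rises by 50% and the outcome difference is zero, whatever the positivity.
- The number advised rises whenever a1/a0 > 8/12 = 0.667. From the plan's 4% in controls, any strategy rate between 2.67% and 4% reads as worse while more patients are advised.
- If the strategy's positivity is 0.8 or 1.2 times control's, the 2.67% becomes 0.04 × 0.08 / (0.12 × 0.8) = 3.33%, or 0.04 × 0.08 / (0.12 × 1.2) = 2.22%.

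**4. Would the apparent harm be significant?** Assume 25% positivity, so 20 v 30 positives per PHCU-month. The strategy's rate is (20 × control rate + 10 × rate among the extra positives) / 30. SE = sqrt of the sum over arms of p(1 - p)(1 + (n - 1) × ICC) / (kn), with k PHCUs per side. Going from 60 to 15 per side doubles the SE.

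| Control rate | Extra positives advised at | Strategy rate | z, 60 v 60, ICC 0.029 | z, 60 v 60, ICC 0.2 | z, 15 v 15, ICC 0.029 | z, 15 v 15, ICC 0.2 |
|---|---|---|---|---|---|---|
| 75% | 50% | 66.7% | -3.85 | -2.09 | -1.92 | -1.05 |
| 4% | 2.67% | 3.56% | -0.48 | -0.26 | -0.24 | -0.13 |
| 4% | 2% | 3.33% | -0.73 | -0.40 | -0.36 | -0.20 |
| 4% | 0% (break-even) | 2.67% | -1.53 | -0.84 | -0.76 | -0.42 |

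In the first row the number advised per PHCU-month goes from 15 to 20.

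**5. Case mix alone (illustration).** Suppose heavier positives are advised at 90% and lighter ones at 40% in both arms, with 16 heavier and 8 lighter in control and 18 and 18 under a strategy. The rates are 17.6/24 = 73.3% and 23.4/36 = 65.0%, although no type of patient is treated differently and more are advised.

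**6. Power on the eligible denominator.** For 4% v 6%, 0.83 (step 2). If instead 25% are positive and 75% of these are advised in both arms, the rates are 0.08 × 0.25 × 0.75 = 1.5% and 0.12 × 0.25 × 0.75 = 2.25%. Then SE = 0.0043, z = 1.75 and power is about 0.42.

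**The case against.** Much can be said for the present definition. Splitting the pathway into screening and follow-through is a recognisable implementation measure, and advice per eligible consultation mixes the two: a strategy that only raises screening would count on both primary outcomes. Every group is asked to screen all adult attenders, and both rates are measured at baseline before allocation is disclosed. The tally sheets record AUDIT-C score, age and gender, so a shift among positives can be seen. A practice that screens only obvious drinkers does badly on the screening rate, and a reader can recover advice per consultation from the counts. All of this stands. It makes the problem visible but does not change what the outcome measures, and no test or interval for advice per eligible consultation is stated.

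Four stronger readings are tempting, and the document does not support them:

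- **That the second primary comparison is not randomised.** PHCUs are the randomised unit and are compared as allocated. What lacks protection is the comparison among screen-positive patients.
- **That the strategies are meant to change who screens positive.** Only an increase in screening is a stated aim; a change in case mix is a plausible inference.
- **That the outcome will show significant harm.** This needs high advice rates and the 60 v 60 contrast. With 4% advised in controls no case worked reaches significance, though that 4% may not have been framed on screen positives. The hypotheses compare strategies with usual care, where a 15 v 15 contrast would give z = -1.92 even in the most adverse row.
- **That the Background prescribes the eligible denominator.** It speaks of those who could benefit, which is neither screen positives nor all attenders. Only the first hypothesis speaks of use; the others speak of rates.

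**Conclusion.** The point holds in this limited form and should be fixed. The brief advice rate conditions on a post-randomisation group, formed by unblinded providers, that every strategy is expected to enlarge. The firmest consequence needs only the plan's 8% v 12% and equal positivity: unchanged follow-through gives 50% more patients advised and no effect on this outcome, and a rate down to two-thirds of control's still means more patients advised. The outcome can therefore be null or negative despite success. The direction and significance of an apparent harm, and any part played by case mix, rest on assumptions and are illustrations only.

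Separately, the stated 120 PHCUs match an advice rate per eligible patient. On the denominator defined under Outcomes, 120 PHCUs give power of about 0.25 to 0.62 for 4% v 6%, under positivity of 10% to 40%, a 60 v 60 contrast, an ICC of 0.029 and one four-week period.

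**What to change.** **Outcomes (Primary outcomes).** Define the primary brief advice outcome as screen-positive patients given brief advice, divided by the same eligible-consultation denominator as the screening rate, times 100. Keep advice per screen positive as a secondary process measure. Report it with the AUDIT-C score, age and gender of positives by group, and state that it conditions on a group formed after randomisation.

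**Sample size.** State which denominator the 4% and 6% refer to, and restate the power on the denominator of the primary outcome.

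**Cost.** No new data are needed, since the counts for both rates are already collected. It is nevertheless a change of primary outcome, not just of wording. The new rate includes screening as a factor, so it does not isolate follow-through, which is why the present rate should stay as a secondary measure. Stated power may also be lower: 0.83 if 4% v 6% is per eligible patient, but about 0.42 for the assumed 1.5% v 2.25%. In that second scenario the present outcome has no difference to detect.

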**Methods/design:**

In a cluster randomized factorial trial, data from Catalan, English, Netherlands, Polish, and Swedish primary healthcare units will be collected on screening and brief advice rates for hazardous and harmful alcohol consumption. The three implementation strategies will be provided separately and in combination in a total of seven intervention groups and compared with a treatment as usual control group. Screening and brief intervention activities will be measured at baseline, during 12 weeks and after six months. Process measures include health professionals’ role security and therapeutic commitment of the participating providers (SAAPPQ questionnaire). A total of 120 primary healthcare units will be included, equally distributed over the five countries. Both intention to treat and per protocol analyses are planned to determine intervention effectiveness, using random coefficient regression modelling.

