### Statistical methods

Because of the hierarchical structure of the data (individual providers nested within PHCU nested within country), we will perform multilevel analyses of the screening and advice rates to examine the effect of the implementation strategies in comparison with the controls. The intention to treat analyses will include all participating providers (see above). Per protocol analyses will include only actively participating providers (see above). In all the analyses, we will use exposure to the implementation strategy as co-variate. Exposure is defined as positive if the providers meet the following criteria: financial—the PHCU received the financial reimbursement; e-BI—the provider handed out at least one referral card; and T&S—the provider attended the two face-to-face educational meetings. If these criteria will not be met, the exposure will be defined as negative.

Analyses will be performed in SAS V9.2 and based on mixed effects model (PROC GLIMMIX and PROC MIXED). We will use a random intercept model with fixed variables.

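### The per protocol set depends on screening recorded after allocation is disclosed, so its estimate for the screening rate is open to bias whose direction depends on the contrast

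*Protocol article*

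**What the plan says.** Under Primary outcomes, the Protocol article defines actively participating providers as those participating providers "who completed at least one tally sheet or computerized record during one of the measurement periods". Statistical methods turns this group into an analysis set: "Per protocol analyses will include only actively participating providers". The companion set is wider: "The intention to treat analyses will include all participating providers".

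The same outcomes section says that "Screening and brief advice will be measured at five timepoints": one baseline period, three blocks during implementation and one follow-up period. Randomization and blinding states that research teams and units learn the allocation only once baseline data are collected, and are unblinded from then on.

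On the record itself, "The tally sheets include AUDIT-C scores"; Catalonia uses electronic patient records instead. The outcome is defined thus: "The screening rate will be calculated as the number of completed screens divided by the total number of consultations of all patients eligible for screening", per participating provider and multiplied by 100.

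On the role of the two analyses, the Abstract says: "Both intention to treat and per protocol analyses are planned to determine intervention effectiveness". The article does not rank them.

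**The concern.** A per protocol set is normally defined by whether the allocated intervention was delivered or received. Here the criterion is whether the provider ever produced the record from which the screening outcome is counted. A provider with no record in any period is one with zero recorded screening throughout, and that provider is dropped. Four of the five chances to qualify arise when the provider already knows the allocation.

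The strategies are meant to raise screening activity. If they succeed, fewer providers stay at zero in the strategy arms than in control, and the rule removes a different share of each arm. The remaining groups are then no longer comparable by randomization. At stake is an estimate, planned as evidence of effectiveness, that can differ from intention to treat for reasons unrelated to adherence.

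**Working it through.** **Is the criterion adherence to a strategy?** Statistical methods defines exposure separately: reimbursement received by the unit, at least one referral card handed out, both face-to-face meetings attended. The per protocol set uses none of these. A training-arm provider who attended both meetings but recorded nothing is excluded; one who attended neither but recorded one screen is included. Control providers have no strategy to adhere to and are dropped for inactivity alone.

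**Inputs for an illustration.** The documents give no active share, so there is no stated figure to reproduce, and the sample size figures do not enter. All of the following are assumptions:
- Share active at baseline, equal in both arms: a = 0.50.
- Share of baseline-inactive providers who start later: s = 0.10 (control), 0.50 (strategy).
- Screening rate of established active providers: 8 per 100 consultations (the planned control rate under Sample size, borrowed for convenience).
- Screening rate of new starters, r: 8 or 4 per 100.
- The strategy has no effect on providers already active, consultations per provider are equal, and a provider without a record counts as zero in intention to treat.

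**Formulas.**
- Share retained: p = a + (1 − a)s. Control 0.50 + 0.50 × 0.10 = 0.55; strategy 0.50 + 0.50 × 0.50 = 0.75.
- Rate over all providers: F = 8a + (1 − a)s·r.
- Per protocol post-baseline level: F / p.
- Per protocol change from baseline: (1 − a)s·r / p, because baseline-active providers do not change and starters go from 0 to r.

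**Results (per 100 consultations).**

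| Contrast | Starters at 8: control, strategy, difference | Starters at 4: control, strategy, difference |
|---|---|---|
| All providers | 4.40, 6.00, **+1.60** | 4.20, 5.00, **+0.80** |
| Per protocol, level | 4.40/0.55 = 8.00, 6.00/0.75 = 8.00, **0.00** | 4.20/0.55 = 7.64, 5.00/0.75 = 6.67, **−0.97** |
| Per protocol, change | 0.40/0.55 = 0.73, 2.00/0.75 = 2.67, **+1.94** | 0.20/0.55 = 0.36, 1.00/0.75 = 1.33, **+0.97** |

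**Range.** I took a = 0.30, 0.50 and 0.80, start fractions (control, strategy) of 0.10/0.30, 0.10/0.50 and 0.20/0.60, and starters at 8 or 4, giving 18 combinations.
- All-provider effect: +0.16 to +2.24.
- Per protocol level contrast: 0.00 in all nine combinations with starters at 8; −0.18 to −1.40 in the nine with starters at 4.
- Per protocol change contrast: +0.18 to +2.79. Algebraically it equals the all-provider effect times a / (p_control × p_strategy). In the example the factor is 0.50 / (0.55 × 0.75) = 1.21. It exceeds 1 in 16 of the 18 combinations. The exceptions are the two with a = 0.30 and starts of 0.20/0.60, where it is 0.30 / (0.44 × 0.72) = 0.95.

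**The case against.** A reader might infer that the rule simply removes the effect of getting inactive providers to start. The definition does not support that. A provider who starts in any period is kept; only those who never record anything are dropped. A provider active only at baseline also stays in, with later zeros. The start effect vanishes or reverses in post-baseline levels but survives, usually inflated, in change from baseline. Statistical methods specifies a random intercept model without saying how baseline enters, so no single direction of bias can be claimed.

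A reader might also infer that the plan gives the two analyses equal standing. It does not say so; it leaves them unranked, and an article may leave ranking to the full protocol or analysis plan. The point rests on the definition that the article does state.

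Three further objections stand:
- Every unit, in every arm, is asked to screen all attending adults. Recording something is therefore a minimal compliance criterion common to all arms, while exposure to a strategy is handled by a covariate. This explains the definition but does not stop retention from differing by arm.
- The argument covers the screening rate only. The brief advice rate is divided by screen positives, so a provider with no record has no defined rate under either population, and the rule removes no provider who has one.
- Intention to treat over all participating providers is planned and keeps the start effect for screening. The fault is confined to the companion analysis.

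**Conclusion.** The concern holds in limited form. As written, the per protocol set selects on recorded screening in a window that lies mostly after allocation is disclosed, and it can retain different shares of each arm. Its estimate for the screening rate is open to bias, and the direction depends on a contrast that the article does not specify. On the assumed figures, a true +1.60 becomes 0.00 or +1.94, and a true +0.80 becomes −0.97 or +0.97.

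These figures show the mechanism and do not predict this trial. They rest on assumed active shares, on a strategy that acts only by starting inactive providers, and on new starters who screen no more than established ones. If nearly all providers are active in every arm, the bias is small. The intention to treat result and the brief advice rate are not called into question.

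**What to change.** - State that conclusions on effectiveness for the screening rate rest on the intention to treat analysis of all participating providers.
- Label the analysis of providers active in any period as descriptive, and report the proportion of participating providers active, by arm. That proportion shows directly whether a strategy got providers started.
- If an active-provider comparison free of post-allocation selection is wanted, define it by at least one record in the four-week baseline period, which is collected before disclosure, and label it a baseline-active subgroup.

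The cost is a change of wording; no new data and no change to the sample size are needed. The baseline-active subgroup has a real downside. It is smaller, and by design it excludes every provider whom a strategy gets to start. In the illustration above it would give 8 v 8 per 100, a difference of 0. It answers a narrower question and cannot replace intention to treat or serve as a repaired per protocol analysis.
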